**C. Secondary efficacy outcome variables and statistical analyses**

The following efficacy outcome variables will also be evaluated for HIV-seronegative children. The analyses will include the graded ARI case definitions listed in VIII C.2. The primary outcomes (see above) and secondary outcomes 1 and 2 below will also be evaluated for children infected with HIV (see E below) as secondary analyses. The power for these analyses will depend on the number of outcome cases meeting the definition for inclusion in the particular analysis.

1. All invasive pneumococcal disease, including nonvaccine serotypes, in children who complete three doses of vaccine. This analysis will be performed using the methods and case definitions described above for the primary outcomes and include all first episodes of pneumococcal disease, regardless of serotype.

2. Vaccine-serotype invasive pneumococcal disease in children who complete at least two doses of vaccine, the first episode of disease occurring at least 14 days after the 2nd dose of vaccine. Exact binomial tests, including children who meet the case definitions described above and who have received either 2 or 3 doses of the vaccine, will be used as for the primary outcome analyses.

3. Vaccine-serotype invasive pneumococcal disease in all children who have received at least one dose of vaccine in the study regardless of immunization status (intent-to-treat analysis for vaccine-serotype pneumococcal disease). The intent-to-treat analysis will include the first episode of vaccine-serotype pneumococcal disease in children who were initially randomized into the study and received at least one dose of study vaccine and regardless of the number of vaccine doses they eventually received or whether they voluntarily withdrew from the study and were lost to follow-up. The null hypothesis of no difference between the two groups in all randomized chldren will be tested.

4. Vaccine immunogenicity will be assessed in a random sample of 400 children over the study period, or 200 children per lot of study vaccine introduced into the trial. The geometric mean titers of the antipneumococcal antibodies and 95% confidence interval of the vaccinated children will be determined and the distribution will be examined using reverse cumulative plots. The different response distributions of vaccine lots will be compared.

5. Vaccine safety will be assessed by adverse reaction reports of all study children, including all hospitalizations. Report rates of the vaccinated and control group will be compared using Fisher’s Exact test.

6. The relationship between vaccine efficacy and antibody response will be evaluated based on the distribution of antipneumococcal antibodies in vaccinated and control children.

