**D**. **Treatment period**

Each study subject will receive three injections of either pneumococcal conjugate vaccine or placebo, administered concurrently with TETRAMUNE®, OPV, and Hep B. The injections will be administered at approximately 6, 10, and 14 weeks of age, with a minimum interval of 3 weeks between each dose and all three doses must be completed by 9 months of age. Children not returning within 1 week of the appointed time for the second or third vaccinations will either be telephoned or visited at home.

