**F. Follow-up**

**1. Vaccine Safety**

Following each vaccination, the child will be monitored at the clinic for approximately 15 minutes for any immediate local and/or systemic reactions. The parent/guardian will also be asked to observe for untoward effects which might occur within one week of vaccination. If the parent/guardian has concern, they will be asked to report these reactions to the study nurse as soon as possible. Any child with a clinical event of concern to the parents will be evaluated by the study nurse or other medical personnel. In the event that the child is hospitalized, the parent will be asked to contact the investigator immediately. Study pediatricians will also be conducting daily surveillance for hospitalization of study participants. Participation in the vaccine study will be noted on the child’s Road to Health card, which is presented at hospital visits.

All efforts will be made to obtain follow-up information on deaths which occur outside of the hospital through death notifications, cemetary records, etc..

The frequency of adverse events following vaccination will be assessed for both the placebo and treatment groups.

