**D. Assessment of vaccine safety**

1. All children will be observed for 15 minutes following vaccine administration for any immediate local and/or systemic reactions at the clinic by qualified study personnel. Parents will also be advised to return to the clinic immediately should the child develop reactions of concern to the parent. Follow-up will occur on all allergic reactions, severe local reactions within 72 hours of vaccination, as well as on all seizures occurring within 4 weeks of vaccination.

2. The study pediatricians will conduct daily surveillance for hospitalization of study children (see Section VIII) at Chris Hani Baragwanath Hospital. All deaths, life-threatening events, and unexpected events related to the vaccine will also be investigated. Efforts will also be made to follow-up all deaths occurring outside of the hospital through death notifications and cemetery records. Prior to implementation of the study, meetings will be held with the pediatricians of the hospitals to inform them of the nature of the study and the need to notify study investigators should they see study participants. Reminder notices will be placed in the appropriate wards and the children’s Road to Health cards will also be clearly labelled so as to indicate their participation in the study. The majority of mothers bring the Road to Health card when the child is hospitalized.

3. The Safety Monitoring Committee (see Section XIV) and WLVP will review safety data quarterly during the trial. All severe, life-threatening reactions or the deaths of study participants, regardless of the etiology, and unexpected events felt by the study physicians to be vaccine-related will be reported monthly to the members of the Committee as well as to WLVP. Quarterly reporting to WLVP will include all of the above reactions as well as seizures or changes in neurological status within one month of vaccination and severe local or systemic reactions or allergic reactions within 72 hours of vaccination. A report of the incident cases of pneumococcal disease will be provided to the Safety Committee quarterly.

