**A. Primary outcome variables**

1. Cases (see Section VIII for case definition) of vaccine-serotype pneumococcal invasive disease in children who have completed the three-dose series per protocol.

2. Cases (see Section VIII for case definition) of radiologically-confirmed hospitalized pneumonia in children who have completed the three-dose series per protocol.

Outcomes will qualify for the primary analysis of they occur at least 14 days after the third dose of vaccine/placebo. Outcome ‘1' will be the basis for the vaccine efficacy estimate. Since the prevalence of radiographically-confirmed severe pneumonia may be several-fold higher than that of culture-confirmed pneumococcal invasive disease (to be estimated from the ongoing pneumonia surveillance study) and the mortality rate from severe pneumonia is probably high (to be estimated from the ongoing pneumonia surveillance study), outcome ‘2' will be used to assess the effectiveness of the vaccine in reducing the overall pneumonia disease burden and its impact on public health as well as to estimate the proportion of severe pneumonia caused by pneumococci of vaccine serotypes.

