The current estimate of the incidence of invasive pneumococcal disease in children under the age of 2 years in Soweto is 160/100,000 child years [12]. Assuming that 70% of the disease cases are due to the vaccine serotypes, the vaccine-serotype disease rate is 112 cases per 100,000 child years. Based on this estimate of disease rate and the assumption that the true vaccine efficacy is 70%, approximately 19,231 child years follow-up per treatment group will be needed to accrue 28 cases of vaccine-serotype disease in HIV-uninfected children. The annual birth cohort in Soweto is approximately 24,000 infants, 4% (960) of whom would be expected to be HIV-infected. Allowing for loss to follow-up, the entire birth cohort over a two year period will be recruited to reach the targeted enrolment goal. The study is expected to accrue 28 cases of vaccine-serotype disease in HIV-uninfected children in approximately 32 months. Approximately 29,533 child years of follow-up per treatment group, expected in approximately 39 months, will be needed to accrue 43 cases. A more accurate estimate of the disease rate is expected to be obtained prior to the start of the study from the prospective cohort study currently underway in Soweto.

The rate of hospitalized pneumonia (Primary Outcome ‘2') will be compared between the treated and the control group using a Poisson regression, with age category and calendar month of the third dose (season category) as possible stratification variables. An estimate of the rate reduction and its confidence interval will be obtained from the Poisson regression. Multiple events of an individual will be included in the rate estimates. The null hypothesis is that there is no rate reduction and will be tested based on the Poisson regression with a two-tailed  = 0.05. An analysis to compare the number of children with at least one event between the two groups will also be performed.

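### The safety comparison of all hospitalizations sets no post-dose window and does not separate efficacy-outcome admissions, so vaccine benefit can offset an excess of other admissions.

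*Protocol*

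**What the plan says.** Protocol Section IX.C, item 5 fixes the safety measure: "Vaccine safety will be assessed by adverse reaction reports of all study children, including all hospitalizations". It then fixes the comparison: "Report rates of the vaccinated and control group will be compared using" Fisher's exact test. No other between-arm safety test is named for all study children. Section V.F.1 says only that adverse event frequency will be assessed in both groups, and the log-rank mortality comparisons in Section IX.E cover HIV-infected children alone.

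Hospital admissions are captured without a post-dose limit. Section VI.D states: "The study pediatricians will conduct daily surveillance for hospitalization of study children".

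Periods after a dose do appear elsewhere. Section V.F.1 says: "The parent/guardian will also be asked to observe for untoward effects which might occur within one week of vaccination". Section VI.D, item 1 follows up allergic reactions, "severe local reactions within 72 hours of vaccination, as well as on all seizures occurring within 4 weeks of vaccination". These periods govern observation, follow-up and reporting. They are not attached to the comparison in IX.C, item 5.

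Primary outcome 2 in Section IX.A is "radiologically-confirmed hospitalized pneumonia in children who have completed the three-dose series per protocol". Primary outcome 1 is vaccine-serotype invasive disease, which is sought among admitted children (Section VI.E).

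**The concern.** Two separate problems follow from the wording of item 5.

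- **Benefit counts as safety.** Admissions for pneumonia and invasive pneumococcal disease are part of all hospitalizations. If the vaccine works, the total falls for a reason unrelated to harm, and that fall can offset a rise in other admissions.
- **No risk window.** Doses are due at about 6, 10 and 14 weeks of age (Section V.D), while the mean age at pneumonia admission in the surveillance study is 11 months (Section I.H). An early excess caused by injection would be mixed with many later, unrelated admissions.

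At stake is a reassuring result on the named safety test while non-target admissions after vaccination are raised. The efficacy results are not affected.

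**Working it through.** The protocol gives no sample size, power or expected effect for the safety comparison, so there is no safety figure to reproduce. The follow-up figures used below do reproduce. With a vaccine-serotype rate of 112 per 100,000 child-years and 70% efficacy (Section IX.B):

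- 28 / (0.00112 × 1.3) = 19,231 child-years per arm
- 43 / (0.00112 × 1.3) = 29,533 child-years per arm

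**Step 1: offset by benefit.** Bronchopneumonia was 30.5% of 1995 ward admissions (Appendix 1), so other causes were 69.5%. The reduction r in these admissions is assumed.

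| r | Fall in all admissions, 0.305 × r | Rise in other admissions that this masks, (0.305 × r) / 0.695 |
|---|---|---|
| 10% | 3.1% | 4.4% |
| 20% | 6.1% | 8.8% |
| 30% | 9.2% | 13.2% |

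**Step 2: dilution.** Assume a 4-week window after each of three doses: 3 × 28 = 84 days. Assume a constant admission rate. The dilution factor is mean follow-up divided by 84 days.

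*From the protocol's child-years.* The two-year birth cohort is about 48,000, or 24,000 per arm.

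- 19,231 / 24,000 = 0.80 years = 293 days, and 29,533 / 24,000 = 1.23 years = 449 days.
- These child-years count from 14 days after dose 3, whereas safety runs from dose 1. Weeks 6 to 14 plus 2 weeks add 10 weeks, or 70 days.
- (293 + 70) / 84 = 4.3, and (449 + 70) / 84 = 6.2. Without the added time the factors are 3.5 and 5.3.

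*From calendar dates.* With uniform enrolment over 24 months and no deaths or loss, mean follow-up is the study length minus 12 months.

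- Target dates (Section XV): 36 − 12 = 24 months = 730 days; 730 / 84 = 8.7.
- The 39-month figure (Section IX.B): 39 − 12 = 27 months = 822 days; 822 / 84 = 9.8.

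The range is therefore about 4 to 10. With one-week windows every factor is four times larger.

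**Step 3: both together.** Suppose non-pneumonia admissions double inside the windows. The overall change is 0.695 / dilution − 0.305 × r.

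| Dilution | Added by the doubling | Net, r = 10% | Net, r = 20% | Net, r = 30% |
|---|---|---|---|---|
| 4.3 | +16.2% | +13.1% | +10.1% | +7.0% |
| 6.2 | +11.2% | +8.2% | +5.1% | +2.1% |
| 8.7 | +8.0% | +4.9% | +1.9% | −1.2% |
| 9.8 | +7.1% | +4.0% | +1.0% | −2.1% |

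**Step 4: effect on power.** Take an assumed 10% cumulative admission risk, 24,000 per arm, no vaccine benefit, and a rate ratio of 1.25 for admissions inside the windows. At 8.7-fold dilution, approximate power is 80% for the windowed comparison and 18% over all follow-up. At 3.5-fold it is 99% and 73%.

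**The case against.** The strongest reply is that windows and tables by diagnosis usually belong in the statistical analysis plan, which is not at hand, and that item 5 is a summary sentence which blocks no such tables. The reference to report rates could mean rates by type of event, not one total. Pneumonia admissions are compared separately (Sections IX.B and IX.D, item 3), so a reader would see that benefit beside the total. The Safety Monitoring Committee reviews safety data quarterly, receives deaths and life-threatening events monthly, can break the code, and writes its own final report (Sections VI.D and XIII.B).

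Part of this stands. The committee is a real safeguard, reactions tied to the 72-hour and 4-week periods are less diluted, and all-cause hospitalization is a legitimate net measure. But item 5 is not silent. It names a measure and a test, and efficacy can pull that measure down. The separate pneumonia comparisons test pneumonia, and neither they nor the committee's stated remit isolates admissions for other causes.

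A reader might also infer stronger claims that the documents do not support:

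- That the protocol prescribes counting over the whole follow-up. This is inferred from the missing window.
- That 72 hours and 4 weeks are the protocol's windows for admissions. In Section VI.D they apply to reactions and to seizures.
- That dilution is about ninefold and a doubling shrinks to about +2%. Those values need 24 months' mean follow-up, a constant admission rate and a 20% pneumonia reduction. The protocol's own child-years give clearly less dilution.

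**Conclusion.** The point holds as a weakness in how the safety comparison is defined. It does not show that a wrong safety conclusion will follow. The direction is clear: efficacy lowers the measure, and the missing window weakens any short-term signal.

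The size is illustrative. The 30.5% share is clinical bronchopneumonia among 1995 ward admissions, not radiologically confirmed pneumonia in trial children. Nothing in the protocol supports a particular reduction in it, hence the range of 10 to 30%. The 4-week window for admissions and the constant admission rate are assumptions too. Higher admission rates in early infancy would reduce the dilution. No single figure from the tables should be used as a headline.

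The change is a cheap improvement that is worth making.

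**What to change.** Amend Section IX.C, item 5 as follows, for all children with at least one dose, by arm:

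1. Compare hospitalizations for causes other than pneumonia and invasive pneumococcal disease within pre-set windows after each dose. One option is to extend the 72-hour and 4-week periods of Section VI.D to admissions, ending each window at the next dose.
2. Make the same comparison over full follow-up.
3. Report pneumonia and pneumococcal admissions separately, counted from the first dose, so that a harmful effect on them would also be seen and the parts add up to the total. State which definition of pneumonia is used for the split.
4. Keep all-cause hospitalization as a net-effect summary.

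No new data are needed. Dose dates are in the immunization registers (Section VI.A), and admissions are documented through hospital surveillance and the case forms (Section VI.E). The cost is a few more tables. The downside is several comparisons instead of one, with fewer events in each.

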**D. Other analyses**

Additional data analyses will include the following:

1. The impact of vaccination on the proportion of cases of invasive pneumococcal disease that are penicillin-resistant. The proportion in each vaccine group will be compared by Chi-square or Fisher’s Exact test.

2. The efficacy of the vaccine against invasive pneumococcal disease due to individual serotypes will be evaluated using exact binomial tests as described above if there are at least 6 cases of disease caused by an individual serotype.

3. The impact of the vaccine in the total pneumonia disease burden will be assessed by comparing the incidence of pneumonia requiring admission in vaccinees and controls using an exact binomial test.

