**B. Statistical analyses for the primary outcome variables**

Efficacy of the vaccine will be estimated by comparing the incidence rates of vaccine-serotype invasive pneumococcal disease (Primary Outcome ‘1') between the recipients of three doses of the vaccine and placebo. Efficacy will be estimated as (1-RR) x 100%, where RR is the ratio of the incidence rate of the treated group versus that in the control group. With individualized randomization of a large cohort at a 1:1 allocation ratio, the follow-up time in the treated and control groups should be equal. The rate ratio can, therefore, be estimated as the ratio of the number of cases in the treated group versus that in the control group.

An exact two-sided 95% confidence interval for vaccine efficacy will be estimated, based on the binomial distribution for the number of cases among vaccinees, given the total number of cases and the ratio of follow-up time in placebo recipients to follow-up time in vaccine recipients. The statistical power for this analysis depends on the true efficacy and the number of accrued cases. For power calculations, we assume the true efficacy against vaccine-serotype invasive disease is 70% and that the ratio of follow-up times is 1. Then 28 cases are required for an 80% probability that the lower limit of the 95% confidence interval for efficacy will be greater than 0 (i.e., to reject the hypothesis of no efficacy); for an 80% probability that the lower limit will be greater than 20% 43 cases are required. We plan to enrol study infants until 28 HIV-uninfected vaccine-serotype cases have been accrued for the primary analysis and then continue surveillance until a total of at least 43 cases have been accrued. The following cases splits, out of the 28 cases, can lead to rejection of the null hypothesis.

| Control Cases | Treated  Cases | Estimate of vaccine  efficacy (%) | Lower 95% Confidence  Limit of VE (%) |
| --- | --- | --- | --- |
| 28 | 0 | 100 | 85.9 |
| 27 | 1 | 96.3 | 77.5 |
| 26 | 2 | 92.3 | 69.2 |
| 25 | 3 | 88.0 | 60.6 |
| 24 | 4 | 83.3 | 51.4 |
| 23 | 5 | 78.3 | 41.5 |
| 22 | 6 | 72.7 | 30.6 |
| 21 | 7 | 66.7 | 18.6 |
| 20 | 8 | 60.0 | 5.1 |

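### The 6-case minimum is a sound limit for testing individual serotypes, but as a condition for estimating efficacy at all it depends on a count that the vaccine itself lowers

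*Protocol*

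**What the plan says.** Protocol Section IX.D (Other analyses), item 2, states: "The efficacy of the vaccine against invasive pneumococcal disease due to individual serotypes will be evaluated using exact binomial tests as described above", subject to the condition "if there are at least 6 cases of disease caused by an individual serotype". It does not say whether the 6 cases are counted in one arm or both, why 6 was chosen, or which population is meant.

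The method it refers back to is in Section IX.B. It is an exact two-sided 95% interval for efficacy, calculated as follows: "based on the binomial distribution for the number of cases among vaccinees, given the total number of cases". Because that method conditions on the total, a total over both arms is the natural reading of the 6, but this is an inference.

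The planning figures are also in Section IX.B: "we assume the true efficacy against vaccine-serotype invasive disease is 70% and that the ratio of follow-up times is 1"; "28 cases are required for an 80% probability that the lower limit of the 95% confidence interval for efficacy will be greater than 0"; "for an 80% probability that the lower limit will be greater than 20% 43 cases are required". The vaccine has nine serotypes (Protocol Summary). The protocol gives no breakdown of expected cases by serotype.

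**The concern.** The condition is a count observed after randomisation, and the vaccine is meant to reduce it. Take two serotypes equally common in the control arm. The one the vaccine prevents produces fewer cases in total and is less likely to reach 6. A 3:3 split would be evaluated; a split of 5 control cases to 0 vaccine cases would not.

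What is at stake is how the serotype results read. For a vaccine with nine separately coupled components, readers will want to know which ones appear to work. A list selected in this way leans, at equal incidence, towards the less-protected serotypes and says nothing about most of the others.

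**Working it through.** **1. The plan's own figure.** At 70% efficacy and equal follow-up, a case is a vaccinee with probability 0.3/1.3 = 0.2308. With the exact conditional binomial method, 28 cases give 82.2% power for a lower limit above 0; 25, 26 and 27 cases give 79.8%, 76.4% and 72.8%. The 28 is reproduced, as are the lower limits in the 28-case table. With "the vaccine-serotype disease rate is 112 cases per 100,000 child years", 28/(0.00112 × 1.3) = 19,231 and 43/(0.00112 × 1.3) = 29,533 child years per group, as stated.

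**2. What 6 means for the test.** The most favourable split of N cases is N:0. Its two-sided exact p is 2 × 0.5^N. The upper limit for the vaccinee share is u = 1 − 0.025^(1/N), and the lower efficacy limit is 1 − u/(1 − u).

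- N = 5: p = 0.0625; u = 0.522; lower limit −9.1%.
- N = 6: p = 0.031; u = 0.459; lower limit +15.1%.

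Six is therefore the smallest total that can reject.

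**3. How efficacy changes the chance of being evaluated.** Let c be the expected control cases of a serotype. The expected total is c(2 − VE), and the chance of evaluation is P(Poisson(c(2 − VE)) ≥ 6). For c = 5 the means are 10, 6.5 and 5 at VE 0, 70% and 100%.

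| c | VE 0 | VE 70% | VE 90% | VE 100% |
|---|---|---|---|---|
| 3 | 55% | 20% | 12% | 8% |
| 4 | 81% | 42% | 28% | 21% |
| 5 | 93% | 63% | 47% | 38% |
| 6 | 98% | 79% | 65% | 55% |
| 10 | 100% | 99% | 96% | 93% |

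**4. How many of the nine would be evaluated.** This assumes that the 28 and 43 cases of the primary outcome apply, and 70% efficacy throughout.

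- *Equal shares.* Mean total per serotype is 28/9 = 3.1 or 43/9 = 4.8. P(≥ 6) is 9.6% or 34.5%, so 9 × 0.096 = 0.9 or 9 × 0.345 = 3.1 serotypes.
- *Unequal shares*, an illustrative split of 25, 20, 15, 12, 10, 8, 5, 3 and 2%. At 28 cases: 0.699 + 0.488 + 0.247 + 0.124 + 0.065 + 0.027 + 0.003 + 0 + 0 = 1.7. At 43 cases: 0.956 + 0.858 + 0.624 + 0.412 + 0.263 + 0.135 + 0.023 + 0.002 + 0 = 3.3.

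**5. How far the list leans.** Suppose efficacies of 95%, 70% and 45% (assumed), three serotypes each, at 43 expected cases, that is 43/1.3 = 33.1 expected control cases.

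- *Equal shares* (c = 33.1/9 = 3.68): chance of evaluation 19%, 35% and 50%. Mean true efficacy of those evaluated is (0.193 × 95 + 0.345 × 70 + 0.504 × 45)/1.042 = 63%, against 70% for all nine.
- *The unequal split above*, efficacy unrelated to share: 27%, 36% and 44%. The mean is (0.270 × 95 + 0.364 × 70 + 0.442 × 45)/1.076 = 66%.

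**6. Incidence against efficacy.** With 33.1 expected control cases, a serotype with a 20% share and 100% efficacy has mean total 6.6 and is evaluated with probability 65%. One with a 5% share and no efficacy has mean 3.3 and is evaluated with probability 12%.

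**7. Validity of the test.** Given a total of at least 6, the expected vaccinee share at 70% efficacy stays 0.2308. With no efficacy, false rejection in favour of the vaccine is 1.1% to 1.5%, below the nominal 2.5%. With c = 4, the chance of a significant result at VE 70%, 90% and 100% is 8.5%, 15.8% and 21.5%, with or without the rule.

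**The case against.** The strongest defence is that the rule is a correct feasibility limit for a test. It uses the total, on which the exact test already conditions, and sets it at the lowest value where rejection is possible. Each serotype result it lets through is valid. That stands in full. A reader might infer that the rule biases the tests or discards significant results; steps 2 and 7 show that it does neither.

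A reader might also infer that a fully effective component could never be shown. That is wrong: a 6:0 split qualifies, and with 10 expected control cases a fully protected serotype is evaluated 93% of the time.

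Nor can one say without qualification that the best-protected serotypes are the likeliest to drop out. That holds only at equal incidence. Step 6 gives a counterexample, and Section I.G suggests incidence is unequal: its recent list of common serogroups in children at the study hospital does not include 4, 5, 9 or 18.

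Finally, the condition may be read as limiting only the test, with descriptive counts left to an analysis plan that is not at hand. The protocol indeed does not say that counts by arm will be withheld. But what it makes conditional is the evaluation of efficacy, with no provision for serotypes below 6. Being unable to reach p < 0.05 is a reason to withhold a test, not an estimate and its interval.

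**Conclusion.** The point holds as a minor improvement to an exploratory analysis. Six total cases is a sound threshold for testing. Used to decide which serotypes receive an efficacy estimate, it selects on a count that the vaccine lowers, and at equal background incidence it favours the less-protected serotypes. The contrast is large for a single serotype with about 5 expected control cases (38% against 93%) and modest for the list as a whole (mean true efficacy 63% to 66% against 70%, under the assumed efficacies).

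This rests on four assumptions: that the 6 counts both arms; that the 28 to 43 cases planned for the per-protocol, HIV-uninfected primary outcome also apply to item 2, which names no population; that counts are Poisson; and that serotype shares are as illustrated, since the protocol gives none. The direction at equal incidence does not depend on the shares; the number of serotypes evaluated does. The primary efficacy conclusion is not affected.

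**What to change.** In Section IX.D, item 2, replace the condition with three statements.

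- For each of the nine vaccine serotypes, report cases by arm, estimated efficacy where calculable and the exact 95% confidence interval, whatever the count.
- Apply the exact test only to serotypes with at least 6 cases in both arms combined, name the population, and give the reason: 6:0 gives p = 0.031, 5:0 gives p = 0.0625.
- State that a sparse serotype that is untested or not significant is not evidence of no efficacy. At exactly 6 cases and 70% efficacy, the only rejecting split in favour of the vaccine, 6:0, has probability (1/1.3)^6 = 0.21.

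Requiring 6 control cases instead would remove the dependence on efficacy but evaluate fewer serotypes: with 4 expected control cases, 21.5% at every efficacy, against 41.9% at 70% efficacy under the present rule.

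The cost is a nine-row table with very wide intervals for sparse serotypes; a 5:0 split, for example, would show 100% with a lower limit of −9.1%. No other analysis changes.
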